
### Sample size calculation

Based on our center’s TMS results to date, patients start TMS treatment with an average MADRS score of 25.4 (SD 7.3), which decreases significantly to 18.4 (SD 9.9) after 2 weeks of treatment with standard rTMS and to 14.1 (SD 10.7) after 4 weeks of treatment. Participants enrolled in the study would be expected to have similar improvements in MADRS with aTMS treatment.

This study is powered to test the primary aim, i.e., a significant reduction in MADRS scores from baseline to end week 3, in the overall study sample. Based on the MADRS scores cited above for baseline (25.4 ± 7.3) and end week 4 (14.1 ± 10.7) time points, detecting a similar significant change after a course of aTMS would require a sample of 12 participants (alpha 0.5, 95% power). However, given the lack of data on the efficacy of aTMS in an Asian population, and to give a better estimate of response and remission rates, we anticipated that 60% of those recruited will drop out before the end of the trial with an unequal allocation ratio of 2:1, we thus aim to recruit 40 subjects in the delayed start arm and 20 subjects in the immediate start arm for a total of 60 subjects.

No prior data exist on the comparative effects of delayed response with immediate treatment of aTMS (or TMS), we will also explore the aim that non-responders to a 1-week course of aTMS will have a higher chance of response to a change in aTMS from L 5 Hz DLPFC TMS to R 1 Hz DLPFC for depression. This study will produce pilot data for 2nd and exploratory aim, informing the power analysis for a future clinical trial if results reject a null hypothesis.

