## Methods

### Objectives

The primary aim of this study is to test the symptomatic efficacy of aTMS trial protocol. The 2nd aim is to compare the symptomatic efficacy of the early-start aTMS treatment group and delayed-start aTMS treatment group in patients with a DSM 5 Major Depressive Episode. The exploratory aim is to test whether the non-responders to a 1-week course of aTMS will have a higher chance of response to a change in aTMS than repeated the same aTMS modality (from 5 Hz L DLPFC aTMS to 1 Hz R DLPFC aTMS).

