### Hypothesis

We hypothesize that accelerated 5 Hz L DLPFC rTMS is effective for the treatment of depressive symptoms with regard to reducing the MADRS scores from baseline to end week 3 in the overall study sample.

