### Statistical analysis

Clinical, demographic characteristics and mood, cognitive, and QoL scores will be tested for any differences at baseline between the two randomized groups using *t test* or *chi-square* test wherever appropriate. The effect size of aTMS will be assessed by the proportion of response rate, which was defined as “Response: ≥50% MADRS score decrease from baseline” and “Non-response: <50% MADRS score decrease from baseline”. “Remission” is defined by score of 10 or less on MADRS score. Changes in mood and other ratings from baseline to each follow-up time point will be assessed with paired *t* test followed by repeated-measures analysis of variance (*ANOVA*)*.* Statistical tests will be two-tailed.

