### Strengths and limitations

This trial has several strengths. The delayed start phase will decrease the likelihood of a significant placebo response by subjects who respond to increased attention in a clinical trial. The psychological response elicited by placebos is very specific depending on various factors such as the patient’s expectations, feelings, beliefs, volition, and hope for improvement [52, 53]. Growing placebo response is an important issue of antidepressant therapy for clinical trials involving patients with MDD [54–57]. A recent meta-analysis summarized from 61 large randomized clinical trials (RCTs) suggesting that there is a large placebo response for rTMS trial regardless of the modality of intervention [58]. In our trial, we designed a 1-week delay of treatment to possibly mitigate the placebo effect of active treatment by rTMS. However, it remains unclear whether this delayed-start phase may also reduce the anti-depressant effect of active treatment as some opinions exist that placebo response may be a component of therapeutic response to rTMS in MDD [58]. Patients will receive treatment as usual during the delayed week without coming to rTMS clinic. During the delayed phase, there is still weekly MADRS assessment and this will help patients maintain good adherence with the trial as the patients will keep informed about the study and establish a positive relationship and engagement with clinical staff.

We proposed a 2-week follow-up period after patients have been treated with compact 20 sessions of rTMS. Several open-label large-scale RCTs have shown that some patients with standard treatment of rTMS experienced a delayed response and required 4–6 weeks of stimulation before showing adequate response [12, 59–61]. Similarly, although the accelerated form of rTMS treatment with multiple sessions conducted daily may induce a rapid anti-depressant effect, there are still possibilities that some patients remain non-responding or poor-responding immediately after completion of prescribed sessions of rTMS. Therefore, 2 weeks follow-up period was proposed in this study to allow us to identify this specific group of patients with delayed responses.

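### The claim that aTMS is effective rests on an uncontrolled pre-post MADRS change pooled over both arms, which would reach significance from background improvement alone; the randomised week-1 contrast should carry any efficacy statement

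*Protocol article*

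**What the plan says.** In the protocol article, Objectives puts efficacy first: "The primary aim of this study is to test the symptomatic efficacy of aTMS trial protocol". The Hypothesis section says that "accelerated 5 Hz L DLPFC rTMS is effective for the treatment of depressive symptoms", to be judged by "reducing the MADRS scores from baseline to end week 3 in the overall study sample". The Sample size calculation follows suit: "This study is powered to test the primary aim, i.e., a significant reduction in MADRS scores from baseline to end week 3". Its figure of 12 participants is built on a single-group fall from 25.4 (SD 7.3) to 14.1 (SD 10.7).

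The Statistical analysis section says: "Changes in mood and other ratings from baseline to each follow-up time point will be assessed with paired" t tests, and then by repeated-measures ANOVA. The only comparison between the randomised groups that it names is of baseline characteristics.

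Patients are nevertheless randomised to immediate aTMS or to one week of usual treatment without TMS, and both arms have weekly MADRS by a blinded rater. Of this contrast, Objectives says: "The 2nd aim is to compare the symptomatic efficacy of the early-start aTMS treatment group and delayed-start aTMS treatment group". The Sample size calculation describes it as a source of pilot data.

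Strengths and limitations cites a meta-analysis finding a large placebo response in rTMS trials. It also lists as a strength: "The delayed start phase will decrease the likelihood of a significant placebo response by subjects who respond to increased attention in a clinical trial".

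**The concern.** The paired test asks whether the mean change differs from zero. It does not ask whether patients improve more with aTMS than without it. Entry requires a MADRS of at least 20, usual treatment continues, and the article itself expects a substantial placebo response. Scores should therefore fall in the pooled sample whether or not stimulation adds anything, and rejecting the hypothesis of no change cannot support the conclusion that the treatment is effective.

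The randomised comparison that would remove several of these explanations is collected but carries no weight in the efficacy conclusion. This matters because the article foresees its findings informing treatment guidelines and routine practice.

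**Working it through.** **Inputs from the article.** Baseline 25.4 (SD 7.3); week 4 on standard rTMS 14.1 (SD 10.7); week 2 on standard rTMS 18.4 (SD 9.9); 12 participants for 95% power; 60% drop-out; 20 early-start and 40 delayed-start; entry at MADRS 20 or more; "Statistical tests will be two-tailed".

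**Assumptions.** The article gives no pre-post correlation r, background fall or one-week difference between arms. Each is assumed and shown as a range. Alpha is printed as 0.5; 0.05 is used here because 0.5 does not reproduce 12.

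**1. The plan's own figure.** The change is 25.4 − 14.1 = 11.3. The SD of change is √(7.3² + 10.7² − 2r × 7.3 × 10.7). At r = 0.5 this is √(53.29 + 114.49 − 78.11) = 9.47. A paired t test (non-central t, two-sided 0.05) has 96.3% power at n = 12 and 94.5% at n = 11, so 12 is reproduced. A two-sample test of the same 11.3 points, with SD √((53.29 + 114.49)/2) = 9.16, needs 2 × (1.960 + 1.645)² × 9.16² / 11.3² = 17.1, that is 18 per arm. The stated 12 is therefore a pre-post figure without a comparator.

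**2. Probability of significance if aTMS adds nothing.** The background fall is d and the non-centrality is d√n / SD of change. The SD of change is 11.00, 9.47 and 7.64 at r = 0.3, 0.5 and 0.7. With 60% drop-out, 60 × 0.4 = 24 are evaluable.

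| Evaluable | Background fall | r = 0.3 | r = 0.5 | r = 0.7 |
|---|---|---|---|---|
| 24 | 3 points | 25% | 32% | 45% |
| 24 | 5 points | 57% | 70% | 87% |
| 60 | 3 points | 55% | 68% | 85% |
| 60 | 5 points | 93% | 98% | >99% |

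**3. The part due to the entry rule alone.** Treat 25.4 (SD 7.3) as a normal distribution cut at 20. The cut lies at (20 − 25.4)/7.3 = −0.74, and the ratio of density to upper tail is 0.303/0.770 = 0.394. The selected mean is thus 7.3 × 0.394 = 2.88 points above 25.4, or 28.3. The expected fall on re-rating is (1 − r) × 2.88: 0.3 points at r = 0.9 and 1.4 at r = 0.5. A 1-point fall alone gives significance with probability 7 to 9% at 24 and 11 to 17% at 60 (r = 0.3 to 0.7). Most of a 3 to 5 point fall would therefore have to come from placebo response, usual care and natural course.

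**4. The randomised contrast at the end of week 1.** With SD 9.9 and a baseline correlation of 0.5, the residual SD after ANCOVA is 9.9 × √(1 − 0.25) = 8.57. The standard error is 8.57 × √(1/20 + 1/40) = 2.35 with all patients assessed. It is 8.57 × √(1/8 + 1/16) = 3.71 if the full 60% loss had already occurred.

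| True difference | 20 vs 40 | 8 vs 16 |
|---|---|---|
| 3 points | 24% | 12% |
| 5 points | 55% | 25% |
| 7 points | 83% | 44% |

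Seven points equals the two-week fall on standard rTMS (25.4 − 18.4). That fall is itself uncontrolled, so it is not evidence for a 7-point difference between arms.

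**The case against.** The sponsor can fairly say that the article admits having no sham group, calls the study a pilot and keeps the between-arm comparison as its second aim. An analysis plan that is not shown may also specify a fuller model. The disclosure stands but does not repair the inference: Objectives, Hypothesis and Sample size calculation positively place the efficacy conclusion on the pooled change. Whether that plan contains a baseline-adjusted between-arm analysis is unknown, so its absence is not part of this point.

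A reader might infer that the week-1 contrast is unbiased, or would prove a specific effect of stimulation. The documents do not support that. Patients know whether they are receiving TMS and there is no sham, so expectancy remains. Nor is the control untreated: delayed-start patients receive usual treatment.

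It is also fair that week 1 sits awkwardly with the design, which expects delayed response and follows patients for two weeks after treatment for that reason. And the contrast may be poorly powered, as step 4 shows, although the 60% loss is forecast to the end of the trial and week-1 loss may be smaller.

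Finally, it would go too far to say that the delay does nothing about placebo response. Elsewhere in the same section the claim is hedged, and only delayed-start patients who still meet the entry criteria go on to stimulation, so some who improve early are screened out. The delay does not, however, lessen the response to stimulation itself, and the early-start arm has no delay.

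**Conclusion.** The point holds. As written, a significant primary result would not support the statement that aTMS is effective. For an assumed background fall of 3 to 5 points, the chance of such a result with no aTMS effect is 25 to 87% at 24 evaluable patients and 55 to over 99% at 60, for r from 0.3 to 0.7. The size depends on that assumed fall; the logic does not, since any background improvement raises the error rate above 5%.

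This does not show that aTMS is ineffective, nor that the randomised contrast would settle the question. It shows that the pooled test cannot, and that the week-1 contrast excludes more of the alternative explanations using assessments already planned.

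**What to change.** 1. In Hypothesis, Sample size calculation and Statistical analysis, report the pooled baseline-to-week-3 change as a descriptive estimate with a 95% confidence interval and no efficacy claim.
2. Rest any efficacy statement on the early-start minus delayed-start difference in MADRS at the end of week 1, before the delayed arm is stimulated. Include all randomised patients, whether or not they go on to active treatment, and use ANCOVA with baseline MADRS as covariate.
3. State that this contrast controls for time, usual care and regression to the mean, but not for expectancy, and that it does not capture late response.
4. Do not carry the 95% power over to it. Give its power as a range with the assumptions, as in step 4 of the working, and say that no one-week difference between arms is available.
5. In Strengths and limitations, do not present the delay as reducing placebo response to stimulation. At most, it screens out delayed-arm patients who improve during the delay week.

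**Cost.** No new assessments are needed, because both arms already have weekly blinded MADRS. It is more than rewording, however: the contrast behind the efficacy claim changes, its time point moves from week 3 to week 1, and the stated power becomes less favourable. In a registered trial, the change should be dated and documented before the outcome data are examined.

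### The sample-size paragraph is wrong as printed: alpha 0.5 cannot give 12 patients, and 12 with 60% dropout gives 30 recruits, not 60

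*Protocol article*

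**What the plan says.** All of the calculation stands in the Sample size calculation section of the protocol article. The powered aim is "a significant reduction in MADRS scores from baseline to end week 3, in the overall study sample". The inputs are the centre's own standard-rTMS results, "baseline (25.4 ± 7.3) and end week 4 (14.1 ± 10.7) time points", carried over to the accelerated course by a declared assumption: "Participants enrolled in the study would be expected to have similar improvements in MADRS with aTMS treatment". From these the section concludes that detecting such a change "would require a sample of 12 participants (alpha 0.5, 95% power").

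To move from 12 to the recruitment target, the section mentions the lack of Asian data on aTMS and a wish to estimate response and remission rates better. It continues: "we anticipated that 60% of those recruited will drop out before the end of the trial with an unequal allocation ratio of 2:1". It then concludes: "we thus aim to recruit 40 subjects in the delayed start arm and 20 subjects in the immediate start arm", 60 in total.

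The Statistical analysis section fixes the test and the sidedness. Changes "from baseline to each follow-up time point will be assessed with paired" t tests, and "Statistical tests will be two-tailed". It gives no significance level.

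**The concern.** Significance level, effect, dropout and recruitment target are all stated, and they do not fit together. An alpha of 0.5 is not a usable level, and the sample-size parenthesis is the only place in the article where a level appears, so a reader cannot correct it from another section. The word linking the dropout statement to the 60 recruits presents 60 as a consequence of what precedes it, but no arithmetic in the paragraph leads there. The allocation ratio sits in the same sentence although the powered test pools both arms. The test is at end of week 3, while the effect comes from end of week 4, and the link is not explained.

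What is at stake is traceability. Nobody can tell from the article which level, which SD of change or which evaluable number the sponsor relied on.

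**Working it through.** **Inputs.** From Sample size calculation: baseline mean 25.4 (SD 7.3), week-4 mean 14.1 (SD 10.7), power 95%, dropout 60%, 20 + 40 = 60 recruits. From Statistical analysis: paired t test, two-sided. Not given: the correlation r between baseline and follow-up scores. It is an assumption here and is varied.

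**Step 1. Standardised change.** Mean change = 25.4 − 14.1 = 11.3.

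SD of change = √(7.3² + 10.7² − 2r × 7.3 × 10.7) = √(167.78 − 156.22r).

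At r = 0.5 this is √89.67 = 9.47, so d = 11.3/9.47 = 1.19.

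**Step 2. Number needed for 95% power** (two-sided paired t test, exact noncentral t):

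| r | SD of change | d | n at alpha 0.05 | n at alpha 0.5 |
|---|---|---|---|---|
| 0 | 12.95 | 0.87 | 20 | 8 |
| 0.3 | 11.00 | 1.03 | 15 | 6 |
| 0.5 | 9.47 | 1.19 | **12** | 5 |
| 0.7 | 7.64 | 1.48 | 9 | 3 |

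The plan's 12 is reproduced at two-sided 0.05 with r = 0.5, where 12 patients give 96% power. At alpha 0.5 no non-negative correlation comes near 12; the largest figure is 8. One-sided 0.05 with r = 0.3 would also give 12, but the plan says its tests are two-tailed.

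**Step 3. Dropout.** Recruits = evaluable/(1 − dropout) = 12/(1 − 0.6) = 30. The common mistaken form, 12 × 1.6 = 19.2, rounds up to 20. Neither gives 60. Working backwards, 60 × 0.4 = 24 evaluable, twice the stated requirement. For 60 recruits to shrink to 12, dropout would have to be 1 − 12/60 = 80%.

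**Step 4. Does the primary test lose power?** If only 24 patients were evaluable, power at two-sided 0.05 for the stated change of 11.3 is 98.3% at r = 0 and 99.8% at r = 0.3, and higher still as r rises.

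**Step 5. Precision of a response rate.** The 95% half-width at a 50% rate is 1.96 × √(0.25/n): 28 points with 12 patients, 20 with 24, and 13 (12.7) with 60.

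**Step 6. Sensitivity to the effect size.** Two smaller changes can be built from the section's figures. One is its 2-week value (18.4, SD 9.9; change 7.0). The other is a week-3 value interpolated between weeks 2 and 4 (mean 16.25, SD 10.3; change 9.15), which is an assumption made here. At two-sided 0.05:

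| Effect | n for 95% power, r = 0 / r = 0.5 | Power with 24, r = 0 / r = 0.5 |
|---|---|---|
| Interpolated week 3 | 27 / 16 | 92.5% / 99.7% |
| 2-week value | 43 / 23 | 76% / 96% |

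**The case against.** **The week-4 effect is a defensible choice.** By the article's Background, standard rTMS is one session per working day for 4 weeks, about 20 sessions. The accelerated course is 4 sessions a day on 5 weekdays, also 20 (Treatment at phase 1; Strengths and limitations). Counted from the start of treatment, end of week 3 is one treatment week plus two follow-up weeks, so it comes after a full course. The 4-week result is the dose-matched figure, while the 2-week value reflects about 10 sessions. A reader might infer that the week-2 or interpolated figures are the correct inputs and that 12 is therefore too few. The documents do not support that; these are sensitivity cases. What remains is that the mapping is not explained.

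**The alpha is a misprint.** A reader might infer that the primary test will be run with a 50% false-positive rate. That takes a probable typing error literally. The value stands only in the sample-size parenthesis, the analysis section does not adopt it, and 12 is exactly what 0.05 gives at r = 0.5.

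**Sixty is not presented as dropout inflation alone.** The section also cites better estimation of response and remission. A reader might infer that this purpose fails at the expected dropout. It does not: no precision target is set, and 24 completers still estimate a rate better than 12 (20 points against 28). What stands is that the gain is not quantified and that the step from 12 to 60 is not shown.

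**Twenty-four evaluable is pessimistic.** The 60% refers to loss by the end of the trial, which includes phase 2. Week 3 comes earlier, and the article gives no attrition figure for it.

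**The 2:1 ratio accounts for the 40/20 split.** That is a fair reading, but it does not give the ratio a role in a pooled within-patient test. Nor does this calculation give grounds for changing the allocation, since the early-versus-delayed comparison is described as producing pilot data.

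**Conclusion.** The point holds as an error in the stated basis of the sample size. Two statements are wrong as printed: alpha 0.5, which with the quoted inputs gives 3 to 8 patients for r from 0.7 down to 0, and the step from 12 with 60% dropout to 60, which should give 30. Two further items need explaining: the correlation behind 12 (n runs from 20 to 9 as r goes from 0 to 0.7) and the use of a week-4 effect for a week-3 test. The 2:1 ratio does not belong in the power argument.

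The point does not extend to an underpowered primary test. Even if the full 60% were lost by week 3, the 24 remaining patients would have at least 98% power for the stated effect. This rests on two-sided 0.05 being the intended level, r not being negative, and the declared assumption that aTMS matches the 4-week standard-rTMS change. Only the 2-week effect combined with a low correlation takes 24 patients clearly below 90% power, and that is not the effect the plan assumes.

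**What to change.** In the Sample size calculation section:

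1. Print the level as two-sided alpha 0.05, after the sponsor confirms that this was intended, and repeat it in Statistical analysis.
2. State the correlation or SD of change that the sponsor actually assumed, and show n over a range of correlations. The value of 0.5 used here is back-calculated from the answer and should not be inserted as if it were the sponsor's input.
3. Correct the dropout step to 12 evaluable, 30 recruited, or correct the 60% if that figure is the slip. Say whether the 60% applies by week 3 or by the end of phase 2.
4. Justify 60 separately, by the precision it gives for response and remission: a 95% half-width of about 13 points with 60 patients and 20 with 24, at a 50% rate.
5. Move the 2:1 ratio out of the power argument and give it only as the allocation.
6. Add a sentence on why the 4-week standard-rTMS effect is used for week 3 of aTMS. The smaller effects can be added as optional sensitivity cases.

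The cost is wording and a short recalculation. The recruitment target need not change and no extra patients are needed.

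### The pilot data for the second and exploratory aims are to inform a future trial on condition of significance, in comparisons this study is not powered for

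*Protocol article*

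**What the plan says.** The section Sample size calculation claims power for one aim only: "This study is powered to test the primary aim", a within-patient fall in MADRS over the whole sample. It then says "This study will produce pilot data for 2nd and exploratory aim", and the sentence ends "informing the power analysis for a future clinical trial if results reject a null hypothesis". The same section says that no earlier comparative data exist. It gives no between-group difference and no power for either of these aims.

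It plans 20 early-start and 40 delayed-start patients, and "we anticipated that 60% of those recruited will drop out before the end of the trial". Under Randomization at phase 2, only patients who have not remitted are randomised again, to left or right stimulation. Under Statistical analysis, "Statistical tests will be two-tailed".

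**The concern.** A pilot comparison is useful to a later trial through its estimates: the difference with its uncertainty, the spread, the response rates and the retention. These are informative whether or not a test is significant. The sentence attaches a significance condition to their use, in comparisons for which no power is claimed.

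Such a condition can mislead in two ways. With low power, a true and relevant difference often fails the test and would then not be carried forward. When the test does succeed, the estimate has been selected for being large; if it were then used as the assumed effect of the next trial, that trial would be too small. Both effects depend on the true difference and on how many patients remain.

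**Working it through.** **Significance level.** The plan's own figure is for the primary aim: "would require a sample of 12 participants (alpha 0.5, 95% power". The inputs are baseline 25.4 (SD 7.3) and week 4 14.1 (SD 10.7), so the change is 11.3. The correlation r between the two scores is not given.
- SD of change = √(7.3² + 10.7² − 2r × 7.3 × 10.7). At r = 0.5 this is 9.47.
- A paired t test at two-sided 0.05 and 95% power then needs 12 patients (power 96%), which reproduces the plan. At r = 0.4 it needs 13, and at r = 0.6 it needs 10.
- At alpha 0.5 as printed, r = 0.5 gives 5 patients. The printed value looks like a misprint of 0.05, so 5% two-sided is used below.

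**Second aim, early versus delayed start.** The true difference d, in SD units, is assumed.
- Standard error of the difference = √(1/n₁ + 1/n₂): 0.274 at 20 versus 40. With 60% lost, 60 × 0.4 = 24 remain, which is 8 versus 16 at 2:1, and the standard error is 0.433.
- Power comes from the noncentral t with noncentrality d divided by the standard error. The mean estimate given p < 0.05 comes from simulation.

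| True d | Power, 20 vs 40 | Mean significant estimate ÷ truth | Power, 8 vs 16 | Mean significant estimate ÷ truth |
|---|---|---|---|---|
| 0.3 | 19% | 2.3 | 10% | 3.4 |
| 0.5 | 43% | 1.5 | 20% | 2.2 |
| 0.7 | 71% | 1.2 | 34% | 1.6 |
| 0.9 | 90% | 1.06 | 51% | 1.4 |

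The 8 versus 16 columns are a worst case (see the objection).

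One result needs no assumed effect. The smallest observed difference that can reach significance is the critical t times the standard error, taking the observed SD as 1:
- 20 versus 40: 2.00 × 0.274 = 0.55 SD
- 8 versus 16: 2.07 × 0.433 = 0.90 SD

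With the SDs in the plan ("average MADRS score of 25.4 (SD 7.3") and ("18.4 (SD 9.9) after 2 weeks of treatment with standard rTMS"), 0.55 SD is about 0.55 × 7.3 = 4.0 to 0.55 × 9.9 = 5.4 MADRS points. An accurate estimate of a 0.5 SD difference would therefore fail the condition even with all 60 patients.

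Required sample size varies as 1/d². If the significant estimate were used for sizing at a true 0.5 SD, the next trial would have about (0.5/0.744)² = 45% of the patients needed in the 20 versus 40 case.

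**Exploratory aim, switch versus repeat.** The ceiling is 60/2 = 30 per arm, if nobody remits or drops out. Response of 25% versus 50% is assumed; the results are exact enumeration of Fisher's test.

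| Per arm | Power | Mean significant difference (true 25 points) |
|---|---|---|
| 12 | 14% | 55 points |
| 20 | 27% | 43 points |
| 30 | 41% | 36 points |

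The article does not name the test for this comparison. With the uncorrected chi-square test at 30 per arm, power is 52% and the inflation 1.37-fold. With a true 20% versus 50%, the chi-square test at 30 per arm has 69% power and 1.2-fold inflation.

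**The case against.** The strongest reply is that a loose closing clause is being read as a decision rule. The word 'only' is not in the text, and the condition might govern whether a later trial follows at all. The same section justifies the larger recruitment partly by better estimation of response and remission rates, with no significance condition. This has weight, but that statement concerns rates in the sample as a whole. No sentence lifts the condition for the two comparative aims, and its natural reading is conditional.

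A reader might infer more: that a non-significant result will be taken as no difference, or that the observed estimate will become the next trial's effect size. The article says neither. To inform a power analysis could mean supplying SDs, response rates or retention. The consequence for the next trial's size therefore holds only if the estimate is used in that way.

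A reader might also infer that relevant differences are usually missed and that every significant estimate is strongly inflated. The calculation does not support that in general: at 20 versus 40, a 0.7 SD effect has 71% power and 1.2-fold inflation, and a 0.9 SD effect 90% and 1.06-fold.

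Finally, the 60% dropout is stated for the end of the trial. The contrast with an untreated arm falls at about week 1, when more patients may remain, so 8 versus 16 may not apply there.

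**Conclusion.** The point holds in a limited form and is minor. The article makes use of its pilot data for two aims conditional on significance, in comparisons with no claimed power and no stated effect, and this works against their stated pilot purpose.

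For true differences of 0.3 to 0.5 SD with all 60 patients, the test would miss the difference in about 57% to 81% of trials, and significant estimates would average 1.5 to 2.3 times the truth. For switch versus repeat at 25% versus 50%, Fisher's test would miss it in about 59% of trials even at 30 per arm. For large effects with full retention, little is lost.

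These figures rest on assumed effects, a two-sided 5% level and the stated recruitment. The primary analysis and this trial's sample size are unaffected.

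**What to change.** Delete the closing condition from the last sentence of Sample size calculation. State instead that the estimated differences for both aims with 95% confidence intervals, together with the observed SDs and the response, remission and dropout rates, will inform the future trial whatever the p value. Add that a non-significant result will not be read as no difference. The choice of a relevant difference for the next trial can be left to that trial's protocol.

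The cost is a sentence or two of text, with no new data or patients. The one downside is that these comparisons can no longer be presented as a pass/fail result.
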